#### Secondary outcomes

The difference in health care costs between the control group and MULTI-NUT-MED intervention group will be evaluated in two stages. In the first stage, the share of participants having zero costs is compared by *t* test or similar. In the second stage, the magnitude of strictly positive health care costs is compared by generalized linear models [144]. Quality-adjusted life-years (QALYs) will be computed based on survival, EuroQol-5D-5L data collection, and Danish preference weights [145]. Incremental cost-effectiveness ratio (ICER) will be computed by dividing the difference in development in health care costs from inclusion to 52 weeks after inclusion between groups with the difference in change in QALYs between groups. The ICERs will be bootstrapped and reported with confidence limits from the bootstrapping, in scatter plots, and in cost-effectiveness acceptability curves.

The difference in AOU score change from baseline to 8 weeks after discharge between the control group and pooled intervention group (MED or MULTI-NUT-MED intervention) will be evaluated similarly to the difference in MAI score change.

DNA sequencing of fecal bacteria will be mapped to an integrated catalog of reference genes of the human gut microbiome in order to generate an operational taxonomic unit. Microbial species and gene diversity (the gut microbiome composition) will be calculated with the Shannon index. Differences in the Shannon index between the control group and intervention group will be evaluated by ANCOVA adjusted for baseline values. Gut microbiome diversity will be evaluated by descriptive analyses in relation to dietary components and nutritional status evaluated by MNA-SF and Global Leadership Initiative on Malnutrition (GLIM) criteria.

GLIM criteria will be validated against in-depth nutritional assessments performed independently by two blinded and trained nutritional experts (semi-gold standard). The nutritional assessment will include factors related to nutritional status, e.g., dietary intake, factors impeding nutritional intake, appetite, and disease history including LOS and readmissions, body composition, weight history, biochemistry, and physical and psychological wellbeing. The prevalence of malnutrition will be evaluated with descriptive analyses based on specific combinations of phenotypic and etiologic indicators in the GLIM criteria. Finally, statistical agreement analysis between the three malnutrition classifications (MNA-SF, ESPEN, and GLIM) will be evaluated by agreement analysis at admission and up to 16 weeks after discharge. Based on in-depth nutritional assessments, participants only meeting one or two malnutrition classifications will be compared to participants meeting all three malnutrition classifications.

The association between non-GFR determinants and differences between mGFR and eGFR will be evaluated by linear regression analysis. Overall agreement between chronic kidney disease classification based on mGFR and eGFR will be evaluated by Kappa statistics. Results of pharmacogenetic testing including frequency of gene variations and medication interventions based on these variations will be evaluated by descriptive statistics.

Prevalence of frailty will be calculated at baseline and follow-up using three different screening tools (FRAIL, Fried’s frailty phenotype, and FI-OutRef). The effect of the intervention on change in frailty between the baseline and follow-up will be evaluated by mixed models with frailty as the dependent variable and a random effect on participant number, to account for multiple measurements from the same participant. The effect will be measured as an interaction of group and time. Depending on the goodness of fit it may be necessary to categorize frailty. Overall agreement between frailty classification based on the different screening tools will be evaluated by Kappa statistics and mixed models. If the intervention is determined to have a significant effect on frailty, then the agreement between frailty classifications will only be performed using baseline data.

All additional confirmative outcomes will be evaluated by *t* test, Kruskal-Wallis test, chi-square test, two proportions *z* test, or Friedman’s analysis of variance depending on the distribution of the relevant variable. The analysis will be adjusted for multiple testing. Associations between variables will be evaluated by adjusted multiple regression models, and repeated measurements will be evaluated by mixed models of paired *t* tests or Fisher’s exact test. Missing data on secondary endpoints will be accounted for with multiple imputations as previously described.

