## Methods: participants, interventions, and outcomes

### Overview and trial design

The OptiNAM trial is a single-center block randomized, controlled, observer-blinded, superiority, and explorative trial with two parallel groups. The trial starts upon admission to the ED and includes follow-up visits at 8 and 16 weeks after discharge and a telephone interview at 1 year after discharge in participants with MNA-SF≤11 to collect EuroQol-5D-5L. Figures 1 and 2 and Table 1 provide schematic overviews of the trial design. The trial was initiated on October 15, 2018, and adheres to the Standard Protocol Items: Recommendations for Interventional Trials (SPIRIT) Statement [59]. Trial registration data (Table 1s) and a SPIRIT checklist are provided in the Supplementary material.

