### Sample size

The trial has three primary endpoints that build on mutually independent hypotheses [140]. Therefore, sample size calculations were performed for each endpoint as described below. All sample size calculations are performed for a significance level of 5%, power of 80%, and a dropout rate of 25%. Ethical approval was obtained for the inclusion of 200 participants in total to ensure enough power for all primary endpoints.
1: Based on a *t* test, a sample size of 120 is required to detect a clinical difference of 3 points (SD=5 points [36]) in MAI score change from baseline to 8 weeks after discharge between the control group and pooled intervention group (MED and MULTI-NUT-MED intervention).2: Based on a paired *t* test, a sample size of 62 participants is required to detect a clinically relevant difference of 4.0 mL/min/1.73m^2^ (SD=15, a R=0.73 [141]) between mGFR and eGFR based on the combination of creatinine and cystatin C. GFR is measured at baseline for all trial participants regardless of group allocation.3: Based on a *t* test, a sample size of 130 participants with or at risk of malnutrition is required to detect a clinically relevant difference of 0.15 points [142] (SD=0.27 [143]) in EuroQol-5D-5L score change from baseline to 16 weeks after discharge between the control group and MULTI-NUT-MED intervention group, assuming equal allocation in the two groups.

Given that patients are included independently of nutrition status and approximately 70% of patients are expected to have or be at risk of malnutrition [4], a total of 185 participants is required to achieve a sample size of 130 participants with or at risk of malnutrition.

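### Bootstrap confidence limits on the ICER lose their meaning if the QALY difference straddles zero; net benefit intervals from the same replicates would not

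*Protocol article*

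**What the plan says.** The economic evaluation is described under Secondary outcomes in the protocol article and compares control with MULTI-NUT-MED: "The difference in health care costs between the control group and MULTI-NUT-MED intervention group will be evaluated in two stages". The ICER numerator is the "difference in development in health care costs from inclusion to 52 weeks after inclusion between groups", and it is divided "with the difference in change in QALYs between groups". On the denominator: "Quality-adjusted life-years (QALYs) will be computed based on survival, EuroQol-5D-5L data collection, and Danish preference weights". EuroQol-5D-5L is collected at baseline, at "follow-up visits at 8 and 16 weeks after discharge and a telephone interview at 1 year after discharge in participants with MNA-SF≤11".

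Uncertainty is dealt with in one sentence: "The ICERs will be bootstrapped and reported with confidence limits from the bootstrapping, in scatter plots, and in cost-effectiveness acceptability curves". The article does not mention net benefit and gives no rule for replicates whose QALY difference is zero or negative.

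The same participants are sized under Sample size: "a sample size of 130 participants with or at risk of malnutrition is required", for a "clinically relevant difference of 0.15 points [142] (SD=0.27 [143]) in EuroQol-5D-5L score change" at 16 weeks, with 5% significance, 80% power and 25% dropout.

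**The concern.** A bootstrap interval for a single quantity ranks the replicates and cuts off the tails, so the ranking must run from worse to better. For an ICER it does so only while all QALY differences have the same sign.

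- A negative ratio can come from a replicate that is cheaper and better (dominant) or from one that is dearer and worse (dominated).
- A positive ratio can be dearer and better, or cheaper and worse.
- As the QALY difference passes through zero, the ratio jumps between plus and minus infinity.

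Once replicates lie on both sides of zero, the lower and upper limits mix these cases. A reader could not tell from the printed limits whether the lower end is good news or bad. The interval printed beside the ICER would then mislead, even if every replicate behind it is correct.

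**Working it through.** **1. The plan's own figure.** Two-sample t test, two-sided 5% (sidedness is not stated and is assumed), 80% power, difference 0.15, SD 0.27: 51.8, so 52 per arm and 104 in total. 104 × 1.25 = 130, which is the stated number. With 25% lost, 130 × 0.75 / 2 = 48.75 per arm.

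**2. From a 16-week effect to a 52-week QALY difference.** Take the group difference in EuroQol-5D-5L as zero at baseline, rising linearly to d at week 16. Visits timed from discharge are treated as timed from inclusion.
- Kept at d to week 52: d × (16/2 + 36)/52 = d × 44/52. For d = 0.15 this is 0.127; for d = 0.075 it is 0.063.
- Fading linearly to zero at week 52: d × (16/2 + 36/2)/52 = d × 26/52. For d = 0.15 this is 0.075; for d = 0.075 it is 0.0375.

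**3. Standard error.** SE = SD × √(2/n). The article gives no QALY SD, so 0.15, 0.20 and 0.27 are assumed; the top value borrows the article's SD for the EuroQol-5D-5L change. With n = 48.75, √(2/48.75) = 0.2025 and the SEs are 0.0304, 0.0405 and 0.0547.

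**4. How often zero is in play.** With z = QALY difference / SE and a normal approximation, the expected share of replicates below zero (at the true difference) is Φ(−z). The chance that the 95% QALY interval includes zero is Φ(1.96 − z) − Φ(−1.96 − z). Example: effect kept, SD 0.27: z = 0.127/0.0547 = 2.32, share below zero 1.0%, chance Φ(−0.36) = 36%.

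Results for about 49 per arm, in the order SD 0.15 / 0.20 / 0.27:

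| 16-week effect, course to week 52 | QALY difference | Replicates below zero | 95% interval includes zero |
|---|---|---|---|
| 0.15, kept | 0.127 | 0.0 / 0.1 / 1.0% | 1 / 12 / 36% |
| 0.15, fades | 0.075 | 0.7 / 3 / 9% | 31 / 54 / 72% |
| 0.075, kept | 0.063 | 2 / 6 / 12% | 45 / 65 / 79% |
| 0.075, fades | 0.0375 | 11 / 18 / 25% | 77 / 85 / 90% |
| none | 0 | 50% | about 95% |

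With all 65 per arm and SD 0.27, the SE is 0.0474. The chance is then 24% (0.15, kept) and 65% (0.15, fades).

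**5. What the limits look like.** This is an illustration with assumed values: 48.75 per arm, QALY SD 0.27, QALY difference 0.075, cost SD scaled to 1 unit, cost difference 0.1 unit, cost and QALY uncorrelated. Simulated replicates give percentile ICER limits of about −18 to +23 units per QALY. About 28% of replicates are dominant and 6% dominated, and both groups have negative ratios.

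The same replicates on the net benefit scale, at 5 units per QALY, have mean 5 × 0.075 − 0.1 = 0.275 and SE √[(5 × 0.0547)² + 0.2025²] = 0.340. The 95% interval is about −0.39 to 0.94, and the probability that net benefit exceeds zero is 0.79. That interval is properly ordered, and 0.79 is the height of the acceptability curve at that threshold.

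**The case against.** Four points on the other side deserve weight.

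- **Likelihood.** A reader might infer that the limits will fail, or probably will, at this sample size. The article does not support that. It gives neither a QALY SD nor a 52-week gain, and if the planned effect is kept for a year the chance is at most about 36% over the assumed range. It is roughly even or higher only if the effect fades (unless the SD is small) or is half as large. Fading is at least plausible, since scheduled dietician visits end at week 8 and the therapy and training components by week 16, but the article makes no forecast.
- **Evaluable numbers.** About 49 per arm is the pessimistic end. Secondary endpoints are to be multiply imputed, and costs and deaths come from registers. Imputation does not restore all the lost information, so the truth lies between 49 and 65 per arm.
- **Other displays.** A reader might infer that the plan has no sound account of joint uncertainty. It has: the scatter plot shows the quadrants, and an acceptability curve built from the joint replicates is the probability of positive net benefit at each threshold. This stands. But a curve supplies no interval, and neither display corrects the ICER limits printed beside it.
- **Level of detail.** The article does not say percentile limits, and it may leave interval construction and willingness-to-pay values to a fuller plan. Their absence is no fault. What is fixed in the text is the commitment to limits on the ratio itself, without a condition, and a different way of ranking the same ratios would not remove the sign problem.

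**Conclusion.** The point holds in conditional form. The article commits to confidence limits for a ratio whose replicates have no meaningful order once the QALY difference straddles zero. The chance of that ranges from about 1% to 90% across the assumed non-null cases, and is about 95% with no effect. It depends on an assumed QALY SD, on how long the effect lasts, on the number evaluable and on a normal approximation. The article's own design effect does not rule the problem out unless that effect largely persists for a year or the QALY SD is small. A prespecified interval should be readable whichever way the trial turns out. Because this is a secondary economic analysis, with sound displays already planned alongside, it is a correction worth making and not a threat to the trial's primary conclusions.

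**What to change.** Keep the bootstrap, the scatter plots and the acceptability curves. From the same replicates, report:

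- incremental cost and incremental QALYs, each with a bootstrap interval;
- incremental net monetary benefit with a bootstrap interval, over a stated range of willingness-to-pay values;
- the share of replicates in each of the four quadrants;
- the ICER as a point estimate, with limits only when essentially all replicates lie in the positive-QALY half plane.

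The cost is a few lines of wording, plus the need to state a willingness-to-pay range in advance. No new data, participants or sample size calculation are needed. Settling it before the replicates are seen also avoids a choice made after the fact.

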### Aims

The study involving acutely admitted older medical patients has three primary aims (1) to determine whether a medication review intervention is superior to standard care in improving medication appropriateness from admission to 8 weeks after discharge, (2) to determine the accuracy of eGFR equations based on various biomarkers compared to mGFR at a single-time point, and (3) to determine whether an individualized multimodal and transitional nutritional intervention is superior to standard care in improving the quality of life from admission and 16 weeks after discharge.

The study also has the following secondary aims which are related to the effect of the intervention: (1) to measure differences in polypharmacy, PIM use, and assessment of underutilization between the MED-intervention and standard care from admission to 8 weeks after discharge and (2) to measure of the differences in body weight, protein- and energy intake, mobility, cognition, frailty, the intestinal microbiome, and health care costs between the MULTI-NUT-MED intervention and standard care from admission to 8 and 16 weeks after discharge and 1 year after discharge (only health care costs).

Secondary aims, which are based on baseline data or data from the control group, include assessment of (1) how information from a broad pharmacogenetic test can potentially improve medication prescribing appropriateness; (2) how polypharmacy, PIMs, nutritional status, frailty, and inflammation modify the effect of the MED-intervention on prescribing appropriateness; (3) how non-GFR determinants affects eGFR and how the choice of eGFR equation affects medication prescribing; (4) how the choice of malnutrition classification criteria affects the prevalence of malnutrition; and (5) how different definitions of frailty affect the distribution of patients classified as frail or sub-frail as well as the responsiveness of these methods.

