## Methods: data collection, management, and analysis

### Data collection methods

Depending on the outcome, data collection is performed at baseline (t_1_), 8 weeks after discharge (t_2_), 16 weeks after discharge (t_3_), 1 year after discharge (t_1y_), and at the GFR-measurement (t_GFR_) (Tables 1 and 2).

Data collection is performed by the same assessor whenever possible to minimize variation. All assessors are provided supervised training in data collection by primary investigator [name], [name], [name], [name], or [name] until deemed ready to perform data collection unsupervised. Data are collected in the ED at baseline and in each participants’ home during follow-up. If a participant declines full data collection at follow-up, then they are offered minimal data collection consisting of blood samples, body weight, MNA-SF, EuroQol-5D-5L, blood pressure, heart rate, hand grip strength, and body composition with BIA. If the participant declines minimal data collection, then they are offered to complete any components of data collection that can be performed by telephone interview. A full medication list for each participant is recorded at every follow-up visit, and the patient’s diagnosis codes and laboratory tests are accessed in the patient chart and stored for future MAI and AOU scores assessment. A full medication list for each participant is recorded at every follow-up visit, and the patient’s diagnosis codes and laboratory tests are accessed in the patient chart and stored for future calculation of MAI and AOU scores. A self-reported medication list is obtained by a senior pharmacist through interviewing the participant, and this list is cross-referenced with the Shared Medication Card. If there are any discrepancies between medications reported by the patient and those found in the Shared Medication Card, then the senior pharmacist confirms the medications by contacting the participant’s relatives, home care personnel, or GP. Registry data (see Table 2) are obtained retrospectively.

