## Discussion

The trial has several strengths and limitations. The major strength of the trial is its randomized controlled study design. The control group allows identification of possible effects of the intervention that are beyond a patients’ normal capacity to recover, which is known to be high in acutely admitted older patients [146]. Another strength of the trial is that the intervention is performed in the same setting where it is designed to be implemented. A third strength of the trial is the use of ^99m^Tc-DTPA plasma clearance for determining mGFR, which is accepted as the gold standard in clinical settings. However, many equations to estimated GFR are developed using Inulin (plasma or urinary) clearance as a reference. Quality of life has a broad definition, and many tools to measure different aspects of quality of life exist. The strength in using EuroQol-5D-5L is that it comprises both the physical and mental aspects of the quality of life and is widely used in nutrition research and that it can be used in health economic evaluations.

A limitation to the trial design is the lack of double-blinding, which may introduce performance bias. However, double-blinding is not possible due to the nature of the intervention. Another limitation is the discrepancy in staff attention required for the control group and intervention group. Participants receiving the MULTI-NUT-MED intervention, for example, will likely require more interpersonal interaction, which may bias the results of the trial. A third limitation is that several components of the MULTI-NUT-MED intervention are based primarily on self-reported questionnaires, which most likely leads to the underutilization of the intervention.

In conclusion, this trial will provide new information on strategies for optimizing treatment of inappropriate medication prescribing and malnutrition and provide new knowledge regarding the accuracy of eGFR among older medical patients admitted to the ED.

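### The frailty mixed model with a random participant effect implies equal variances and correlations across one ED visit and two home visits; if that fails, the 8- and 16-week standard errors are wrong, in a direction the documents do not settle

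*Protocol article*

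**What the plan says.** In the protocol article, under Statistical methods, Secondary outcomes, the stated method for change in frailty is "mixed models with frailty as the dependent variable and a random effect on participant number, to account for multiple measurements from the same participant". A further sentence defines how the effect is read: "The effect will be measured as an interaction of group and time". The outcome scale is left partly open: "Depending on the goodness of fit it may be necessary to categorize frailty".

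Under Aims, the comparison covers "mobility, cognition, frailty, the intestinal microbiome, and health care costs between the MULTI-NUT-MED intervention and standard care from admission to 8 and 16 weeks". Table 2 lists frailty at t1, t2 and t3, so there are three visits. Table 1 places t1 within 36 hours of admission. Under Data collection methods, the setting changes between visits: "Data are collected in the ED at baseline and in each" participant's home at follow-up.

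The article names no random slope, residual covariance structure or type of standard error for this model. It gives no SD, visit-to-visit correlation, power or sample size for frailty.

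**The concern.** A single random participant effect in a linear model, with the usual independent residuals, produces compound symmetry: one variance for all visits and one correlation for all pairs. The first visit is made during acute illness and the other two at home weeks later, so there is no particular reason to expect the three pairs of visits to be equally correlated or the three SDs to be equal.

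The group-by-time effect is a difference in change from the ED visit. Its standard error at 8 or 16 weeks should rest on the variance of that particular change. The random-intercept model uses an average over all three pairs of visits instead. When the pairs differ, the interval and p-value for each visit-specific effect are miscalibrated.

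The test also acts as a switch. The same section says that if the intervention is found to affect frailty significantly, agreement between the frailty classifications will be studied on baseline data only. An error in this test would therefore also decide which data enter the agreement analysis.

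**Working it through.** The plan has no figure for frailty to reproduce. The check asks how far the model's standard error departs from the true one under stated assumptions.

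**Inputs from the article.** Three visits and 1:1 allocation. For this comparison, Sample size states that "a sample size of 130 participants with or at risk of malnutrition is required", hence 65 per arm. The significance level is 5%, taken as two-sided. Dropout is 25%, as in Sample size.

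**Assumed inputs.** All SDs and correlations. Write r12, r13 and r23 for the correlations of baseline with week 8, baseline with week 16, and week 8 with week 16.

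**Formulas** (time as a factor, complete data):
- Variance of a within-person difference: v_ij = s_i² + s_j² − 2·r_ij·s_i·s_j.
- The random-intercept model in effect uses the mean m = (v12 + v13 + v23)/3 for every contrast.
- Model SE / true SE = √(m/v12) at 8 weeks and √(m/v13) at 16 weeks.
- True type I error = 2·[1 − Φ(1.96 × ratio)].

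**Worked cases.**
- ED visit less correlated, SDs all 1, r = 0.4/0.4/0.7: v12 = v13 = 1.2, v23 = 0.6, m = 1.0. The ratio is √(1.0/1.2) = 0.913 at both visits, with type I error 7.4%.
- Decaying correlation, SDs all 1, r = 0.6/0.36/0.6: v12 = v23 = 0.8, v13 = 1.28, m = 0.96. The ratio is √(0.96/0.8) = 1.095 at 8 weeks (3.2%) and √(0.96/1.28) = 0.866 at 16 weeks (9.0%).
- Baseline SD 0.7, others 1, all r = 0.5: v12 = v13 = 0.79, v23 = 1, m = 0.86. The ratio is √(0.86/0.79) = 1.043 at both visits (4.1%).

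| Assumed pattern (r12/r13/r23) | 8-week ratio (type I) | 16-week ratio (type I) |
|---|---|---|
| Equal SDs, 0.5/0.5/0.5 | 1.000 (5.0%) | 1.000 (5.0%) |
| Equal SDs, 0.5/0.5/0.6 | 0.966 (5.8%) | 0.966 (5.8%) |
| Equal SDs, 0.4/0.4/0.7 | 0.913 (7.4%) | 0.913 (7.4%) |
| Equal SDs, 0.3/0.3/0.8 | 0.873 (8.7%) | 0.873 (8.7%) |
| Equal SDs, 0.55/0.45/0.65 | 1.000 (5.0%) | 0.905 (7.6%) |
| Equal SDs, AR(1) 0.5 | 1.080 (3.4%) | 0.882 (8.4%) |
| Equal SDs, AR(1) 0.8 | 1.125 (2.7%) | 0.839 (10.0%) |
| Baseline SD 1.3, all r 0.5 | 0.952 (6.2%) | 0.952 (6.2%) |
| Baseline SD 0.7, all r 0.5 | 1.043 (4.1%) | 1.043 (4.1%) |
| Baseline SD 0.7, 0.5/0.5/0.6 | 1.002 (5.0%) | 1.002 (5.0%) |

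**Simulation check.** The model was fitted by REML with 65 per arm and 2,000 runs, first with complete data and then with 15% missing at week 8 and 25% at week 16.
- r = 0.4/0.4/0.7: ratios 0.90/0.90 at 8/16 weeks with complete data (type I 8.1%/8.3%), and 0.92/0.94 with dropout (6.3%/6.4%).
- AR(1) 0.6: ratios 1.11/0.86 with complete data and 1.09/0.86 with dropout.

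**Joint test.** With r = 0.5/0.5/0.7, 0.5/0.45/0.75 and 0.4/0.35/0.8 at equal SDs, the 16-week ratios are 0.93, 0.89 and 0.86. The two-degree-of-freedom group-by-time test rejects in about 5.4 to 6.6% of null trials.

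**The case against.** The strongest reply is that the article names a participant effect but never says it is the only covariance term. Residual structure and type of standard error are commonly left to a full analysis plan, which is not shown. Part of this stands: a fuller plan could add a structure that removes the problem. But the article does state its device for within-person dependence and the purpose of that device. The point therefore concerns a stated choice and what it implies.

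A reader might infer that the standard errors are too small at both 8 and 16 weeks. The documents do not support that, because they give no frailty SDs or correlations. Decaying correlation makes the 8-week standard error too large, and a smaller baseline SD can make both too large or about right.

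A reader might also take support from the Discussion, which speaks of a "capacity to recover, which is known to be high in acutely admitted older patients". That remark argues for having a control group. It concerns a shift in the mean, which the time effect absorbs, and says nothing about variance or correlation.

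Nor can the point be carried over to the article's general remark that repeated measurements of other outcomes will be evaluated by mixed models, because no random-effect structure is named there.

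Two further objections stand as limits. The article defines the effect as the interaction, does not say how time is coded and lists no separate 8- and 16-week contrasts in the analysis text; the joint test is the less affected one. And if frailty is categorized, the linear formulas above do not apply.

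**Conclusion.** The concern holds in a conditional form. As described, a linear frailty model with a random participant effect implies equal variances and equal correlations across an acute visit and two home visits, and the design gives no reason to rely on that. If the assumption fails, the visit-specific standard errors are wrong.

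The 16-week effect is the most exposed. Under the equal-SD patterns with a less correlated ED visit or with correlation decaying over time, its standard error is about 3 to 16% too small and its type I error about 6 to 10%. The 8-week error can go either way. True equal correlation with equal SDs gives no error, and a smaller baseline SD can remove or reverse it. Inflation of the joint interaction test is mild.

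These sizes rest on assumed SDs and correlations, a continuous outcome and time coded as a factor. Only a secondary outcome is involved: the two primary between-group comparisons use ANCOVA, and no sample size figure depends on this model.

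**What to change.** In the frailty paragraph of Statistical methods, Secondary outcomes, or in the analysis plan if one exists:

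- When frailty is analysed as a continuous score, replace the random participant effect by an unstructured covariance over t1, t2 and t3 with Kenward-Roger degrees of freedom. Treat time as a factor.
- If frailty is categorized, use robust (sandwich) standard errors, because the unstructured residual covariance does not carry over directly.

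This works whichever correlation pattern holds, so the sponsor need not guess it, and fixing it in advance avoids choosing a structure after seeing results. The cost is a line of wording and four extra covariance parameters (six instead of two), which is modest for a comparison planned with 130 participants. The option is available in SAS, which the article already names. No new data are needed.
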